## Results

Descriptive statistics will be used to summarise participants’ sociodemographic details at baseline. Categorical data will be analysed using the chi-square test to determine any significant associations. The normality of the data will be assessed using the Shapiro-Wilk test, while Levene’s test will be applied to ensure the equivalence of variances. To compare outcomes between the VI and normal-sighted groups, either an independent samples t-test or a Wilcoxon rank-sum test will be employed, depending upon the normality of the data. Correlational analysis will be conducted to identify associations between lung function and other outcomes. In phase two, the intervention group will be compared against the control group for all primary and secondary outcomes. We will choose the appropriate parametric or non-parametric test based on the normality of the data. The missing data will be substituted using the predictive mean matching (PMM) imputation method. Analysis will be performed using SPSS version 21 (IBM Corp., Armonk, NY, USA) or RStudio. The study is registered with CTRI and has received Ethics Committee approval in mid-calendar year 2023.

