**Figure 1 FIG1:**
[figure not shown]
Trial flowchart.

This manuscript adheres to the Standard Protocol Items: Recommendations for Interventional Trials (SPIRIT) 2013 guidelines, and the randomized controlled trial (RCT) study will be conducted and reported in accordance with the requirements of the Consolidated Standards of Reporting Trials (CONSORT) statement [17]. Children with VI will be recruited from specialized schools such as Devnar School for the Blind in Hyderabad, Telangana, India. At the same time, children with normal vision will be selected from regular schools. Participants from the phase one study who meet the study criteria will be included in the RCT (phase two).

Objectives of the study

(1) To compare lung function parameters (FVC, FEV₁, and peak expiratory flow rate (PEFR)) between children with VI and normal-sighted children. (2) To compare physical activity, posture, muscle strength, autonomic function, and psychological parameters between children with VI and normal-sighted children. (3) To examine the association between lung function and physical, physiological, and psychological parameters among children with VI. (4) To evaluate the effect of the yoga intervention on lung function, posture, muscle strength, autonomic function, and psychological parameters in children with visual impairment.

Eligibility criteria

The study group will be selected based on the inclusion and exclusion criteria detailed in Table 1.

**Table 1 TAB1:** Inclusion and exclusion criteria. PAQ-A = Physical Activity Questionnaire for Adolescents

	Inclusion criteria	Exclusion criteria
Phase one	Children aged 11-18 years of both genders	Children with any chronic disease
	Children with moderate to severe visual impairment or total blindness	Multiple impairments
	Age-matched normally sighted children	Parents unwilling to provide informed consent
	Being able to understand English	Subjects under any long-term medications
Phase two	Physically low active (mean of total items of PAQ-A <2)	Any injury restricts the practice of yoga.
	-	Exposure to yoga or any exercise six months before the study commenced

Intervention

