Nadi shudhi	21 rounds	4 minutes
Bhramari	18 rounds	3 minutes
Om chanting	-	2 minutes
Deep relaxation technique	1 round	5 minutes
Ending prayer	1 round	1 minutes

Outcome measurements

Demographic details include factors such as age, gender, education level, degree or percentage of VI, parents’ consanguineous marriage, and socioeconomic status (SES). Anthropometric details comprise measurements such as height, weight, and body mass index (BMI).

Primary Outcome

Throughout both phases of the study, lung function parameters FVC, FEV₁, and PEFR will serve as the primary outcomes for group comparisons.

Secondary Outcome

Physical activity, posture, muscle strength, autonomic function (heart rate variability), psychological parameters, and overall physical fitness will be considered secondary outcomes.

Phase one

Barriers to physical activity among children with VI will be assessed using the Physical Activity Barriers Questionnaire for Children With Visual Impairments (PABQ-VI). General physical activity levels will be determined using the Physical Activity Questionnaire for Adolescents (PAQ-A). Outcome measures will also include pulmonary function tests (PFTs) using a spirometer to evaluate lung function, objective assessment of posture using the Posture Screen mobile application, heart rate variability will be evaluated using a portable single-channel ECG module, and upper extremity muscle strength will be assessed using the Lafayette manual muscle test. Depression levels will be gauged using the Children's Depression Inventory (CDI)-2 questionnaire. All variables will be compared between children with VI and those with normal sight, exploring relationships between lung function and factors such as physical activity, posture, heart rate variability, muscle strength, and psychological parameters in children with VI. The schedule for enrollment, intervention, and assessments, following the SPIRIT 2013 guidelines, has been detailed in Table 3 and Table 4.

**Table 3 TAB3:** Phase one trial schedule. VI = visually impaired; PA = physical activity; T0 = enrollment; T1 = baseline assessment of visually impaired children; T2 = baseline assessment of normal-sighted children

Study time points	Enrollment	Baseline assessment	
	T0	T1	T2
		Children with VI	Normal-sighted children
Eligibility screening	X	-	-
Informed consent	X	-	-
Assessments			
Demographic details	-	X	X
Anthropometric details		X	X
Physical activity levels		X	X
Lung function		X	X

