Posture assessment		X	X
Heart rate variability		X	X
Upper extremity muscle strength		X	X
Depression		X	X
Barriers to PA		X	-
Functional performance		X	-

**Table 4 TAB4:** Phase two trial schedule. T0 = enrollment of children with visual impairment from phase one; T1 = intervention to the yoga group for three months; T2 = post-assessment of both groups; T3 = intervention to the control group

Phase two				
Study time points	Enrollment	Intervention	Post-assessment	Intervention
	T0	T1	T2	T3
		Yoga group	Yoga and control group	Control group
Eligibility screening	X	-	-	-
Intervention		X	-	X
Assessments	-	-	-	-
Anthropometric details			X	
Lung function			X	
Posture assessment			X	
Heart rate variability			X	
Upper extremity muscle strength			X	
Depression			X	
Functional performance			X	

Phase two

The outcome measures for the RCT study will encompass lung function, posture assessment, heart rate variability, upper extremity muscle strength, and depression, utilizing the same tools employed before and after 12 weeks of intervention. Functional performance will be evaluated using the 6-Minute Walk Test (6-MWT).

Sample size

Based on an earlier study, the sample size was calculated using GPower software based on PEFR data, with an alpha of 0.05, power of 0.80, and an effect size of 0.8. A 20% attrition rate was incorporated to account for potential dropouts during the three-month yoga intervention in children with VI, who may experience health or participation-related challenges [19].

Recruitment

Participants will be identified by reaching out to special school administrators and teachers. An announcement will be made in the schools to raise awareness about the study and encourage participation. Additionally, teachers and supporting staff will be encouraged to spread the word within school networks. Parents or guardians will also receive information about the study orally during parent-teacher conferences. Recruitment and enrollment of participants will be performed by the study investigator.

Randomization and blinding

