Lung function	Pulmonary function test will be conducted using an NDD Easy on-PC spirometer, following the standards established by the American Thoracic Society/European Respiratory Society for lung function testing. The test will include standard spirometry measures such as FVC, FEV1, FEV1/FVC ratio, and PEFR, among others. The technician will provide a demonstration on how to perform the test and offer clear instructions throughout the procedure. Three reproducible manoeuvres will be obtained in a sitting position, and the highest values will be documented and used for analysis [20]
Heart rate variability	The ECG signal will be recorded using a portable single-channel ECG module. This module, of the plug-and-play variety, can record any one of the bipolar leads (Lead 1, 2, 3) ECG at a rate of 8,000 samples per second. The RR interval obtained from the portable HRV module will be as reliable as the gold standard Biopac MP36 [21]. Following 10 minutes of rest in a supine posture, limb lead 2 ECG will be recorded for 10 minutes in a noise-free environment
Isometric muscle strength	The Lafayette manual muscle tester system (Model 01165, Lafayette Instrument Company, Indiana, USA) will be used to objectively quantify isometric muscle strength. Standardized dynamometer placements and test measurement procedures will be employed to acquire data for shoulder internal rotation and shoulder external rotation. Three successive trials will be conducted with a 10-second rest between each trial in a sitting position. The maximum value obtained will be selected for analysis. The Lafayette hand-held dynamometer demonstrates good to excellent reliability and validity for measuring isometric muscle strength [22]
General physical activity levels	The general physical activity levels will be assessed using the Physical Activity Questionnaire for Adolescents, a self-administered 7-day recall tool designed to evaluate the extent of moderate to vigorous physical activity performed. The reliability and validity of the tool are good and are sensitive to gender differences [23]. This is one of the tools widely used among adolescents and visually impaired adolescents to assess physical activity
Posture	The Posture Screen mobile application will be used to assess posture during the standing position objectively. This application demonstrates strong rater reliability and has shown preliminary evidence of construct validity [24]

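### Phase one age-matches the sighted children, but the planned unpaired tests ignore age: conservative if the matching is real, less precise either way, with a modest loss of power

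*Protocol article*

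**What the plan says.** Table 1 (Eligibility criteria, phase one) admits "Children aged 11-18 years of both genders" and describes the comparison group as "Age-matched normally sighted children". It does not say whether matching is one to one, by frequency, or only to the same age range.

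The Results section fixes the phase-one comparison: "To compare outcomes between the VI and normal-sighted groups, either an independent samples t-test or a Wilcoxon rank-sum test will be employed". The choice between the two tests rests on normality alone. For this comparison the section names no pairing, stratum or age term.

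The outcomes concerned are stated under Primary Outcome: "lung function parameters FVC, FEV₁, and PEFR will serve as the primary outcomes for group comparisons". For spirometry, Table 5 says that "the highest values will be documented and used for analysis"; it names no percent-predicted value or age-standardised score.

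The Sample size section calculates from PEFR data "with an alpha of 0.05, power of 0.80, and an effect size of 0.8". It ties the inflation to the yoga trial: "A 20% attrition rate was incorporated to account for potential dropouts during the three-month yoga intervention in children with VI". It gives no number of children for either phase.

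**The concern.** Matching on a variable that predicts the outcome makes the two groups' results move together. If FVC, FEV₁ and PEFR rise with age, two groups with the same age mix share that part of the variation, and it cancels from the difference in means. An independent-samples t-test or rank-sum test does not take this into account. It judges the difference against the full mixed-age spread, as though the two sets of ages had been drawn separately.

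Objective 1 rests on this comparison. At stake are the width of its confidence intervals, the calibration of its p-values, and some power. The issue is distinct from confounding by sex or height, because it would arise even if the groups were identical on both.

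**Working it through.** **Inputs.** From the article: alpha 0.05, power 0.80, effect size 0.8 and 20% attrition (Sample size). Assumed, because the article does not give them: two-sided testing; age-outcome correlation r from 0.3 to 0.8; total SD of 1; equal numbers of sighted and VI children. There is no stated sample size to reproduce.

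**Step 1: a plausible phase-one size.** The exact two-sided t calculation for 0.8 SD gives 26 per arm (power 0.807). With attrition, 26 / 0.80 = 32.5, so 33. These are sizes for one arm of the yoga trial. The text below Figure 1 and the caption of Table 4 say that the trial's children come from phase one, so the phase-one VI group must fill both arms: 2 × 26 = 52, or 2 × 33 = 66. It must be larger still if some children fail the phase-two criteria on low activity or on previous yoga or exercise.

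**Step 2: type I error and interval width under matching.** The true variance of the mean difference is about 2(1 − r²)/n, while the test uses 2/n. So:

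- true alpha = 2[1 − Φ(1.96/√(1 − r²))]
- interval width relative to the correct one = 1/√(1 − r²)

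Example, r = 0.5: √0.75 = 0.866; 1.96/0.866 = 2.263; alpha = 0.024; width ratio 1.15. Neither expression depends on n.

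| r | alpha, formula | alpha, simulated | width ratio |
|---|---|---|---|
| 0.3 | 0.040 | 0.04 | 1.05 |
| 0.5 | 0.024 | 0.023 | 1.15 |
| 0.6 | 0.014 | 0.014 | 1.25 |
| 0.7 | 0.006 | 0.007 | 1.40 |
| 0.8 | 0.001 | 0.001 | 1.67 |

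The type of matching hardly matters. With age explaining 30% or 50% of the variance, simulated alpha is 0.019 or 0.007 for exact pairs, 0.021 or 0.008 for frequency matching by year, and 0.021 or 0.009 for matching within one year. The rank-sum test under exact pairs gives about 0.017 or 0.006. A paired or age-adjusted analysis stays near 0.05.

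**Step 3: power at 0.5 SD under matching.** Let z = 0.5√(n/2), which is 2.872 at n = 66 and 2.550 at n = 52.

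- planned test: Φ((z − 1.96)/√(1 − r²))
- age-adjusted model: Φ(z/√(1 − r²) − 1.96)

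Example, n = 66, r = 0.5: Φ(0.912/0.866) = 0.854 against Φ(3.317 − 1.96) = 0.913, a loss of 5.9 points.

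| r | n = 66: planned / adjusted / loss | n = 52: planned / adjusted / loss |
|---|---|---|
| 0.3 | 83% / 85% / 2 | 73% / 76% / 3 |
| 0.5 | 85% / 91% / 6 | 75% / 84% / 9 |
| 0.6 | 87% / 95% / 8 | 77% / 89% / 12 |
| 0.7 | 90% / 98% / 8 | 80% / 95% / 15 |
| 0.8 | 94% / 100% / 6 | 84% / 99% / 15 |

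Simulating the t-tests themselves gives losses within about one point of these at 66 and within about two at 52, where the largest is about 17.

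**Step 4: power at 0.8 SD under matching.** The same formulas with z = 0.8√(n/2) give at least 98.7% for the planned test at n = 52 and 99.7% at n = 66. The loss is under half a point.

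**Step 5: if only the age range is shared.** With both groups drawn from the same age distribution, the planned test's alpha is about 0.05. Its power at 0.5 SD is Φ(z − 1.96): Φ(0.912) = 82% at 66 and Φ(0.590) = 72% at 52, whatever r is. An age term still raises power to about the adjusted values in Step 3.

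**The case against.** **The matching may be nominal.** Age-matched appears once, as an eligibility criterion, with no ratio, caliper or quota, and recruitment is by announcement in schools. If it means only the same age range, the type I error is right. This stands: the calibration point is conditional. The loss of precision is not, provided the outcome depends on age.

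**The correlation is assumed.** This stands too. At r = 0.3 the effect is small, and for secondary outcomes unrelated to age it is near zero. It would also nearly vanish if percent-predicted lung function were analysed. Table 5 names no such value, but does not rule one out.

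**The error is in the safe direction.** It is: the estimated difference is not biased by it and false positives do not increase.

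**A stronger reading to avoid.** A reader might take 33 per group as the phase-one size and infer that a moderate deficit would probably be missed. At 33 per group and 0.5 SD, the planned test has about 52% power and loses 13 to 39 points for r = 0.5 to 0.8. The documents do not support that. Thirty-three is the derived size of one yoga-trial arm, and phase one has to supply two. At 66 per group under matching, the planned test has about 83% power or more at 0.5 SD. At 0.8 SD, the only effect size the article states, it exceeds 80% even at 26 per group.

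**Conclusion.** The planned tests do not fit an age-matched design. If matching is individual or by frequency, intervals are 1.05 to 1.67 times as wide as they should be and true type I error lies between about 0.04 and 0.001 for r = 0.3 to 0.8. With matching and a 0.5 SD difference, the power loss against an age-adjusted model is about 2-8 points at 66 per group and 3-17 points at 52; at 0.8 SD it is negligible. If only the age range is shared, p-values are calibrated and the cost is precision alone.

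These sizes rest on the assumed correlation, on equal groups, and on phase one being just large enough to fill both trial arms. This is an inefficiency, and a miscalibration if matching is real. It is not a threat to validity, and the documents do not show that phase one is likely to miss a moderate deficit.

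**What to change.** In the Results section, replace the phase-one independent-samples tests with a linear model of each outcome on group with age as a covariate, or with a paired or matched-set analysis if children are matched one to one. Report the group difference and its 95% confidence interval from that model. State in Table 1 which kind of matching is meant.

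The age-adjusted model improves precision for age-dependent outcomes under individual matching, frequency matching or a shared age range, so the choice need not wait for that clarification. Age is already taken from school records (Table 5). The cost is a sentence of wording and one degree of freedom, or keeping pair identifiers if a paired analysis is used. No extra children or measurements are needed.

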Depression symptoms	Depression will be assessed using the 28-item Children’s Depression Inventory-2 questionnaire. Each item provides three response options: 0 for the absence of symptoms, 1 for mild or probable symptoms, and 2 for definite symptoms. A higher score indicates a higher level of depressive symptoms. It is a reliable and well-validated tool for assessing depressive symptoms [25]
Barriers to physical activity	The Physical Activity Barrier Questionnaire-Visually Impaired (PABQ‑VI) short version will be utilized to assess barriers to physical activity among individuals with visual impairments. The PABQ‑VI is a reliable and valid tool for assessing personal, social, and environmental barriers to physical activity in subjects with visual impairments [26]
Functional performance	Functional performance will be evaluated using the 6-minute walk test, conducted in accordance with the standards outlined by the American Thoracic Society (ATS Statement: Guidelines for the Six-Minute Walk Test) [27]
Demographic and physical health assessment	Socioeconomic status will be assessed using the modified Kuppuswamy socioeconomic scale updated for 2021. It classifies families into 5 groups: upper class, upper middle class, lower middle class, upper lower, and lower socioeconomic class [28]. Information regarding consanguineous marriage among children’s parents and the degree of visual impairment and age of the children will be collected from school records. Height will be measured using a stadiometer, while body weight will be measured using a digital scale. Body mass index will be calculated as weight (kg) divided by height squared (m²)

Ethics and dissemination

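### The phase-one lung-function comparison is matched on age only and tested without adjustment, so any sex or height imbalance enters the reported disparity

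*Protocol article*

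**What the plan says.** All references are to the Protocol article.

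- **Outcomes.** Under Outcome measurements, "lung function parameters FVC, FEV₁, and PEFR will serve as the primary outcomes for group comparisons", in both phases. The first item under Objectives of the study is to compare these three measures between the two groups of children.
- **Groups.** Table 1 admits "Children aged 11-18 years of both genders" and describes the comparison group as "Age-matched normally sighted children". VI children come from special schools; "children with normal vision will be selected from regular schools" (Study design and setting). No matching or quota on sex or body size is stated.
- **Measurement.** Table 5 says that three reproducible manoeuvres are obtained and "the highest values will be documented and used for analysis". It does not name litres, percent predicted or z-scores as the analysis scale.
- **Covariates.** Gender and socioeconomic status are among the demographic details, and "Height will be measured using a stadiometer" (Table 5). Table 3 schedules demographic and anthropometric data in both groups.
- **Analysis.** The Results section says that, between the VI and sighted groups, "either an independent samples t-test or a Wilcoxon rank-sum test will be employed, depending upon the normality of the data". It gives the sociodemographic data a descriptive summary and applies chi-square tests to categorical data. It does not use sex, height or age in the lung-function comparison.

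**The concern.** In a non-randomised comparison of children from two kinds of school, nothing in the design makes the sex mix or stature of the groups alike. Lung volumes in this age range vary with age, sex and body size. The article names a test that cannot take these into account, and states no standardised scale that would do so beforehand.

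Two things follow. First, a difference between the groups in the share of boys or in mean height passes into the contrast that the Abstract presents as a health disparity linked to VI. It could produce an apparent deficit where there is none, or mask a real one. Second, even with balanced groups, the variation from age, sex and height stays in the residual, so the comparison is less precise than the collected data allow.

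This goes beyond detail that a condensed article leaves to a fuller document. The article states the test for the primary outcomes of phase one, and a better one can replace it using data already scheduled. Strengths and limitations mentions uncontrolled social support but not sex or body size.

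**Working it through.** **1. Sample size to work with.** The article prints no N for either phase. Its Sample size inputs are effect size 0.8, alpha 0.05 and power 0.80; sidedness is not stated, so two-sided is assumed. The normal approximation gives n = 2(1.960 + 0.842)²/0.8² = 24.5, so 25 per group. The exact t calculation gives 26 (power 0.807). With 20% attrition, 26/0.8 = 32.5, so 33. These inputs are tied to the yoga trial, so 26 and 33 are only indicative for phase one. I add 100 per group as an arbitrary larger case.

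**2. What bias is plausible.** Every input here is an assumption; none comes from the article.

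- Sex: bias = (difference in proportion of boys) × (boy–girl gap in SD). A 20-point difference and a gap of 0.8 to 1.0 SD give 0.20 × 0.8 = 0.16 to 0.20 × 1.0 = 0.20 SD.
- Height: bias = (height–outcome correlation) × (height gap in SD). A correlation of 0.75, a gap of 3 cm and a height SD of 11 cm give 0.75 × 3/11 = 0.20 SD.

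Over a wider range, sex gaps of 0.5 to 1.0 SD with 10 to 40 points' difference in boys give 0.05 to 0.40 SD. Balanced groups give zero. I take 0.2 SD as a single illustrative value.

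**3. Effect on the error rate.** With no true VI difference and bias b, the two-sample t statistic is noncentral t with 2n − 2 degrees of freedom and noncentrality b√(n/2). For b = 0.2:

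| n per group | noncentrality | rejection rate (nominal 5%) |
|---|---|---|
| 26 | 0.2 × √13 = 0.72 | 10.9% |
| 33 | 0.2 × √16.5 = 0.81 | 12.6% |
| 100 | 0.2 × √50 = 1.41 | 29.1% |

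The bias does not shrink with sample size, so the error rate grows with n. At b = 0.1 the rates at 26 and 100 per group are 6.4% and 10.8%.

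**4. Does adjustment remove it?** A simulation (4,000 replicates per setting, no true VI effect) compared the t-test with a height-adjusted linear model. In the mildest setting (correlation 0.5, height gap 0.25 SD, so bias 0.125 SD) the t-test rejected in 7.7% of replicates at 26 per group and 13.0% at 100; the adjusted model rejected in 4.7% and 4.5%. Over all nine settings run (n of 26, 33 and 100; bias 0.125 to 0.40 SD) the adjusted model stayed between 4.2% and 5.3%. The simulated relation is linear with height as the only confounder, so this shows that the method works when the model is right.

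**5. Precision.** If age, sex and height explain a share R² of the within-group variance, adjustment reduces the standard error by about 1 − √(1 − R²) when the groups are balanced on them. For assumed R² of 0.5 and 0.7 this is 1 − 0.707 = 29% and 1 − 0.548 = 45%.

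**The case against.** The strongest reply is that the article never fixes raw litres. The sentence on highest values is a rule for choosing among manoeuvres, and the Introduction discusses earlier results against predicted values, so the authors know that scale. A t-test on percent predicted would fit the Results section as written. This stands as far as it goes: a reader might infer that unstandardised values are specified, but the article only leaves standardisation unstated. The point therefore rests on a stated unadjusted test with no standardisation stated.

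Second, a reader might infer that phase one claims a causal effect of VI. It does not. The first objective is worded as a comparison, and the Abstract speaks of association. An unadjusted contrast is a legitimate descriptive quantity, and if stature lies on a pathway from VI, adjusting for height removes part of the disparity. This is a reason to report both results. It does not explain why sex mix, which depends on which children are recruited, should be left in the contrast.

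Third, one might say that the age matching is analysed wrongly because both tests treat the groups as independent. The article does not say that matching is pairwise. With frequency matching, independent-sample tests are ordinary practice, and ignoring matching mainly costs precision.

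Fourth, it is tempting to add the sex and height figures to 0.4 SD and quote error rates of 29% at 26 per group and 80% at 100. That double counts: an imbalance in sex itself produces a height difference, and the boy–girl gap in lung volume is partly height. The assumed height correlation across ages 11 to 18 also carries age and sex variation, and age is matched.

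Finally, the chi-square tests could reveal a sex imbalance. They would not correct the lung-function comparison for it.

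**Conclusion.** The point holds in a limited form. The stated phase-one test leaves any sex or height difference in the contrast and leaves variance due to age, sex and height in the error term, although the data to deal with both are scheduled in both groups. Whether the groups will differ, and by how much, cannot be known from the article. The rise from 5% to about 11% (26 per group) or 29% (100 per group) illustrates an assumed bias of 0.2 SD at sample sizes that are not stated for phase one; it is not a forecast.

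A reader might infer that the phase-one result is bound to be wrong, or that the whole study is compromised. The documents support neither: the bias is conditional on imbalance, the calculations cover only the lung-function comparison, and randomised phase two is untouched. This should be fixed, as a nearly free improvement to the primary phase-one analysis.

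**What to change.** In the Results section, replace the two-sample test for phase-one FVC, FEV1 and PEFR by one of the following:

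- a linear regression of each measure on group with age, sex and height, reporting the adjusted difference with a 95% confidence interval; or
- the planned t-test or rank-sum test applied to age-, sex- and height-standardised values, with the reference equations named.

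State the analysis scale in either case. Report the unadjusted comparison alongside, because stature might lie on the pathway from VI. Socioeconomic status belongs in a sensitivity analysis. Frequency-matching the sighted children on sex as well as age is optional; it would limit imbalance at recruitment.

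The cost is revised analysis wording and slightly more analysis work. No new measurement is needed. Sex matching, if adopted, adds a recruitment quota in the regular schools.

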## Materials and methods

Study design and setting

The present study has two phases. Phase one involves a comparative assessment between children with VI and normally sighted children. Phase two is a two-group parallel, randomized waitlist-controlled trial with a 1:1 allocation ratio to investigate the impact of a 12-week yoga intervention on lung function and other factors among children with VI (Figure 1).

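### The phase-two test is left to a normality check, and no use is named for baseline spirometry, age, sex or height; one pre-specified ANCOVA per lung-function outcome would be better and costs nothing

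*Protocol article*

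**What the plan says.** The Results section holds the analysis plan. It says "The normality of the data will be assessed using the Shapiro-Wilk test". For the trial it says "In phase two, the intervention group will be compared against the control group for all primary and secondary outcomes", and then "We will choose the appropriate parametric or non-parametric test based on the normality of the data". An independent-samples t-test and a Wilcoxon rank-sum test are named only for the comparison of visually impaired with sighted children. For phase two no test, model, covariate or change score is named.

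The data for an adjusted analysis are collected:
- **Spirometry.** Under Phase two, outcomes are measured "utilizing the same tools employed before and after 12 weeks of intervention".
- **Body size.** Under Outcome measurements, "Anthropometric details comprise measurements such as height, weight, and body mass index (BMI"). Table 5 describes how height is measured.
- **Age and sex.** Outcome measurements lists both, and Table 1 admits both sexes from 11 to 18 years.
- **Primary outcomes.** FVC, FEV1 and PEFR are all primary in both phases. Table 5 says the highest of the reproducible readings is analysed and mentions no percent-predicted value or z-score.

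Table 4, the phase-two schedule, marks assessments only at T2, after the intervention. Its T0 is the enrolment of children from phase one.

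**The concern.** There are two weaknesses in what the sentence fixes.

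First, what is estimated depends on the data. If the normality check sends FVC to a t-test and PEFR to a rank test, one primary outcome yields a mean difference in litres and another a rank comparison with no difference in L/min. Whether 12-week values or changes are compared is also open. These decisions would be taken after the outcomes are seen.

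Second, no role is given to strong candidate covariates. Among boys and girls aged 11-18, absolute lung volumes can be expected to vary with age, sex and height, and each child's own earlier reading should predict the later one. If 12-week values are compared without these covariates, that variation stays in the error term. What is at stake is the width of the confidence interval and the power for effects smaller than the planned one.

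**Working it through.** **Inputs from the article (Sample size; Study design and setting).** The calculation was done "with an alpha of 0.05, power of 0.80, and an effect size of 0.8", using PEFR. In addition, "A 20% attrition rate was incorporated". The design is a "two-group parallel, randomized waitlist-controlled trial with a 1:1 allocation ratio". No sample size, SD, pre-post correlation or sidedness is given, so there is no stated figure to reproduce.

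**Implied size (assumption: two-sided, two-sample t-test).** Normal approximation: n per arm = 2 × (1.960 + 0.842)² / 0.8² = 24.5, so 25. The exact noncentral-t calculation gives 25.5, so 26. Dividing by 0.8 for attrition: 26 / 0.8 = 32.5, so 33 per arm. (A one-sided test would need 20-21 completers per arm.)

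**Unadjusted power with 26 per arm, comparing 12-week values:**

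| True effect (SD) | 0.8 | 0.7 | 0.6 | 0.56 | 0.5 | 0.4 |
|---|---|---|---|---|---|---|
| Power | 0.81 | 0.70 | 0.56 | 0.51 | 0.42 | 0.29 |

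**Adjusted analyses.** Let r be the correlation between baseline and 12-week value, with equal variances. Relative to the unadjusted outcome variance, ANCOVA leaves 1 − r² and a change score leaves 2(1 − r). A raw effect of 0.5 SD then has standardised size 0.5 / √(1 − r²) or 0.5 / √(2(1 − r)). The values of r are assumptions.

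| r | ANCOVA variance left | Cut | Change-score variance left | Power at 0.5 SD: post value | Change | ANCOVA |
|---|---|---|---|---|---|---|
| 0.5 | 0.75 | 25% | 1.00 | 0.42 | 0.42 | 0.53 |
| 0.7 | 0.51 | 49% | 0.60 | 0.42 | 0.63 | 0.70 |
| 0.8 | 0.36 | 64% | 0.40 | 0.42 | 0.80 | 0.84 |
| 0.9 | 0.19 | 81% | 0.20 | 0.42 | 0.98 | 0.98 |

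Worked line for r=0.8: 1 − 0.64 = 0.36; √0.36 = 0.6; 0.5 / 0.6 = 0.83; power 0.84. For the change score: 2 × 0.2 = 0.40; √0.40 = 0.632; 0.5 / 0.632 = 0.79; power 0.80.

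The effect detectable with 80% power is 0.79 SD unadjusted. With ANCOVA it is 0.69 SD at r=0.5 and 0.48 SD at r=0.8.

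**Simulation (26 per arm, 2,500 runs per setting).** A t or rank-sum test picked by Shapiro-Wilk on 12-week values was compared with ANCOVA on the baseline value.
- *Type I error of the picked test:* 0.050-0.060 across normal and skewed data, so no clear inflation.
- *Normal data, effect 0.5 SD:* picked test 0.41-0.43; ANCOVA 0.52 (r=0.5), 0.69 (r=0.7), 0.91 (r=0.85).
- *Skewed data, effect 0.5 SD, r=0.5:* picked test 0.59, ANCOVA 0.54. At r=0.7 the order reverses: 0.57 against 0.69.

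**The case against.** The strongest reply is that the article is a condensed account. It does not say that phase two uses a two-sample test of 12-week values. It says only that an appropriate test will be chosen, and it says that outcomes are measured before and after. A full protocol or analysis plan may name the model. This stands in part: a reader might infer that the trial discards its baseline data, but the text is silent on this, and a change-score test would use them. It does not dispose of the point, because the normality-based choice is a stated rule. A later plan with one fixed model would have to replace that sentence, not merely add to it.

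Three stronger readings are tempting, and the article supports none of them.
- *Most of the available precision is lost.* That needs r² above 0.5, so r above 0.71, and a comparison of 12-week values. The article gives neither.
- *Any effect below 0.8 SD would probably be missed.* On the implied size, unadjusted power is still 0.70 at 0.7 SD and falls below one half only under about 0.56 SD.
- *The comparison is biased or its error rate inflated.* Chance imbalance under randomisation is not bias and is already reflected in the standard error. The simulations showed no clear type I inflation.

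It is also fair that adjustment does not always win, as the skewed case with r=0.5 shows.

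**Conclusion.** The point holds as an improvement that should be made, not as an error that invalidates the trial. The sentence leaves the choice between a mean and a rank contrast to the data, separately for each of three primary outcomes. It leaves open post value or change, and it assigns no role to covariates the trial already has.

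The size is conditional. Taking r from 0.5 to 0.8, residual variance falls by 25% to 64% if 12-week values would otherwise be compared. The gain is much smaller if changes were intended and r is high, and it may disappear with skewed data and modest r. At the planned effect of 0.8 SD the unadjusted test already has power 0.81, so the benefit lies mainly in smaller effects and narrower intervals. These figures rest on an assumed two-sided t-test, 26 completers per arm, and the assumed r. They also take the stated effect size as referring to 12-week values, which the article does not say.

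**What to change.** Replace the phase-two test-choice sentence in Results with text to this effect:

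*Each lung-function outcome (FVC, FEV1, PEFR) at 12 weeks will be analysed by linear regression (ANCOVA) on arm, the child's own pre-randomisation value of that outcome, age, sex and baseline height. The adjusted mean difference will be reported with its 95% confidence interval. The pre-randomisation spirometry from phase one is the baseline value. A rank-based analysis will be a sensitivity analysis only and will not replace the primary result.*

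The statement about the baseline is needed because Table 4 marks no phase-two baseline assessment. Stratifying the randomisation is a separate, optional matter and is not needed for this fix.

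The cost is one paragraph, with no extra children, visits or measurements. It should be settled before outcome data are examined by group.
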